#### Study population and recruitment

For the RCT, 200 participants who are veterans of the Canadian Armed Forces (CAF) or Royal Canadian Mounted Police (RCMP) will be recruited through various organizations and clinics across Canada. Military and RCMP veterans are groups of interest for this study because they are the specific recipients for health benefits from VAC and are the population of focus for the Atlas Institute for Veterans and Families. A list of organizations and clinics that work with Canadian veterans that are supporting recruitment are provided in **Section 3 of the S1 Appendix**. Screening and study assessments will be conducted virtually out of Sinai Health System in Toronto, Ontario.

Study promotional materials, which include a poster, brochure, and website will be used for recruitment. These materials will be distributed by the organizations and clinics supporting recruitment. Interested participants can self-refer by completing a pre-screener survey that is linked through the study website, which allows them to leave their contact information if they may be eligible. Participants can also directly reach out to the study staff via phone and e-mail information on the promotional materials. Specialized clinics that work with Canadian veterans will also identify eligible participants and refer them directly to the study staff for further screening. Study materials will also be prepared in French for the recruitment of Francophone participants.

#### Screening

A virtual screening visit will involve fully informing potential participants about the study, providing them an opportunity to ask questions, and then obtaining informed verbal consent from those that are interested in participating. For those who consent, there will be a subsequent screening for inclusion and exclusion criteria (shown in **Table 2**), which includes administration of the Mini Neuropsychiatric Interview (MINI), the PCL-5, and the Montreal Cognitive Assessment (MoCA) mini version.

**Table 2 pone.0275774.t002:** Outline of inclusion and exclusion criteria and their justifications.

Criteria	Rationale
**Inclusion Criteria**	
Aged 18 years or older.	The population of interest, Canadian veterans with PTSD, are all adults.
CAF or RCMP veteran.	Military and RCMP veterans are a population that experiences PTSD at rates higher than a civilian population. Furthermore, a significant number of veterans are not connected with care through VAC [3]. SKY has been studied in veteran populations, making Canadian veterans a good target population for this study.
Meet criteria for current PTSD as determined by a score of >38 on the PTSD Checklist-5 (PCL-5) [47].	The PCL-5 is a well-validated, 20-item self-report measure for screening and assessing current PTSD symptom severity according to the Diagnostic and Statistical Manual of Mental Disorders (DSM-5) [2, 47]. A score of 31–33 is a cut-off score that has the highest convergent validity with CAPS-5, the gold standard for assessing PTSD symptom severity [48]. The score of 38 is chosen as a conservative estimate of clinically meaningful symptoms of PTSD and has also been used in a previous clinical trial [37, 46].
**Exclusion Criteria**	
Participation in another concurrent clinical trial.	To limit confounding effects of other trials.
Intention to begin a new course of Behavioral Therapy (e.g., Cognitive Behavioral Therapy including Prolonged Exposure or Cognitive Processing Therapy) during the intervention period.	To limit confounding effects from other treatments during the 6-week intervention period. Participants may be eligible 8-weeks after they complete a formal behavioral therapy program.
Past participation in virtual or in-person SKY.	To limit the study intervention as a confounding variable.
Initiated psychotropic medication within 8 weeks prior to the initial screening. Excluded participants could be re-considered for eligibility after stability on medication was achieved.	To limit confounding effects from pharmacological therapies.
Risk of imminent suicidal intent at screening as per MINI screening and standard tool. Such patients will be advised to visit their local emergency department.	Effects of SKY on more severe health conditions are unknown.
Mental disorders including schizophrenia, bipolar I, psychosis of any type.	
Seizure disorder not well controlled.	
Moderate or severe substance use disorder as per the MINI.	
Neurocognitive impairment as determined by a score of 23 or less on the Montreal Cognitive Assessment (MOCA) mini version [49].	Those with any cognitive impairment may have difficulties fully participating in v-SKY sessions.
Unable to connect to the internet and use Zoom for study assessments and interventions.	Because these interventions will be virtual, it is important for participants to have a stable internet connection and a device with a camera and microphone that supports video calls.
Inability to provide informed consent.	As per ethical norms for research involving human subjects, people who cannot provide informed consent due to capacity/competency reasons, medical reasons, literacy or language limitations, etc. will not be included in the trial.

#### Consent

Research staff will first obtain verbal consent from interested participants. We will obtain formal, signed consent from participants who are screened eligible. Those who are able to provide a signed copy of the consent form will be asked to return it by email; a copy of the completed documentation of verbal consent will be sent via email as an attachment. For participants that are unable to provide a signature (e.g. due to lack of a printer and scanner, or software to add an electronic signature), documentation of verbal consent will serve as the record of obtained consent. Participants may consent to the use of their data for future studies and analyses.

#### Institutional approval and registration

This study has received approval by the Mount Sinai Hospital Research Ethics Board (REB approval number: 21-0275-A) and has been registered on clinicaltrials.gov (NCT05235828).

#### Randomization and allocation

Participants will undergo 1:1 randomization and allocation to the active v-SKY intervention group or a waitlist control (WLC) group using the data management and randomization services available at Sinai Health System. This will be used as a central repository for the generation of randomization codes and will ensure concealment of randomization. A member of the research team not involved in recruitment or evaluations will contact participants with randomization and allocation information to maintain blinding. Participants will be allocated into either the active or WLC arms of cohorts that will be running on a rolling basis. Participants randomized to the active arm will receive the v-SKY intervention in groups of 8–12. Participants allocated to the WLC arm will receive the v-SKY intervention after a waitlist period of approximately 6 weeks. It will not be possible for participants to be blinded to their intervention status, but they will be instructed to not share allocation information with study staff. Separate groups for Francophone speakers will be delivered in French on a rolling basis.

*Trial intervention*. SKY meditation is a standardized intervention that includes relaxation techniques as well as periods of group discussion [34, 46]. This practice incorporates different breathing techniques centered around controlling arousal and attention. Initially, the breathing techniques that are taught are calming and focusing. While progressing through the sessions, breathing exercises are more engaging and energizing, which allows the practitioner to focus more in each moment. Participants will be encouraged to learn all of the techniques that are covered during these sessions and also utilize the techniques that are most appropriate for their personal needs. After some initial training sessions, participants will be encouraged to practice their new SKY techniques in environments and situations that they have been avoiding. They would begin with situations that are less triggering, and progress to more difficult situations. At each group session, participants will describe their experiences and discuss ways to continue to incorporate the SKY techniques into their daily lives, until it reaches a point of being natural to use these skills throughout the day, both in practice, and in application.

Experienced and licensed SKY instructors from the International Association for Human Values and Art of Living Foundation will provide the intervention using the video-calling software, Zoom. Instructors undergo a two-year pre-training program followed by a 16-day residential training workshop, a practicum, and subsequent mentorship program. Upon completion of the mentorship program, instructors can facilitate the SKY intervention on their own and are considered fully certified. Instructors providing SKY training for veterans go through an additional 100 hours of specialized training to meet the specific needs of veterans.

Similar to other studies of SKY for veterans living with PTSD [46], instructors will guide participants through the v-SKY intervention through visual demonstrations and verbal guidance. For the first 5 days, groups will meet for 3-hour sessions, followed by five weeks of 1-hour sessions twice per week (**Table 3**). In total, the intervention will be 15 sessions that run for a total of 25 hours. Sessions will not be recorded.

**Table 3 pone.0275774.t003:** A description of the 6-week Sudarshan Kriya Yoga intervention.

Week 1	Sessions 1–5	Participants will be introduced to SKY meditation and breathing practices. Some of these practices and techniques that are covered include ujjayi or “Victorious Breath,” bhastrika or “Bellows Breath,” “om” meditation chants, and the sudarshan kriya, which involves advanced forms of cyclical breathing. Participants will be assigned homework to practice SKY breathing practices for 5, 10, 15, 20, and then 30 minutes. After these first 5 sessions, participants will be asked to practice SKY breathwork for 30 minutes daily.
Weeks 2–6	Sessions 6, 8, 10, 12, 14	Participants will learn more SKY breathing and accompanying practices.
	Sessions 7, 9, 11, 13, 15	Participants will learn guided meditation and home practice programs to facilitate the continuing practice of SKY.

Attendance and homework logs will be used to monitor adherence to the SKY protocol for each cohort.

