In Canada, the use of complementary and integrative health (CIH) interventions has increased steadily over the last several decades; including CIH interventions for PTSD [21]. The rise of CIH interventions among individuals with PTSD may in part be a response to existing challenges of efficacy and accessibility of PTSD treatments [14, 19]. Among veterans in particular, there has been growing interest in CIH interventions [22], with almost 50% of veterans and active duty personnel using at least one CIH therapy [23]. Promising results for meditation and mindfulness-based interventions have been demonstrated for PTSD and many of its comorbidities. Additionally, these interventions have the added benefit of a strong safety profile [24–26].

CIH interventions are complex interventions that involve numerous components such as meditation and breathing exercises, psychoeducation, and group dynamics [27]. Successful implementation of these practices into new contexts and settings necessitates understanding the perspectives of involved stakeholders, including Canadian veterans, instructors, health professionals, and administrators that work with veterans. The availability of resources, administrative and bureaucratic difficulties with integrating CIH interventions in routine care, and balancing patient preferences are among some of the challenges that stakeholders must consider when implementing CIH therapies into veteran health care [28].

Several CIH interventions have demonstrated therapeutic efficacy for improving PTSD symptoms [29–33]. Over the last decade, numerous studies have demonstrated the effectiveness of Sudarshan Kriya Yoga (SKY), a form of breathing-based meditation, for improving PTSD in veteran populations [29, 34–36]. A recently published RCT suggested non-inferiority of SKY compared to cognitive processing therapy for improving PTSD symptoms in US military veterans [37]. Compared to a waitlist control, SKY has shown an effect size of 1.16 for improvement of PTSD symptoms (95% CI [0.20, 2.04]) [29] with retention rates between 81% and 95% [29, 38]. The beneficial effects of SKY are not limited to PTSD, but extend also to major depressive disorder and generalized anxiety disorder [39, 40].

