### Trial design

Effectiveness will be evaluated with a randomized, waitlist controlled, single-blinded (investigator and data analyst), cross-country trial conducted remotely using video calls with a primary endpoint of changes in PTSD symptom severity. Randomization will be performed with a 1:1 allocation to either the active intervention or waitlist control group. This study will be conducted out of the Sinai Health System together with the Atlas Institute for Veterans and Families, with study promotion and recruitment support from several clinical and community-based organizations across the country. Evaluations of PTSD symptom severity, depression, anxiety, pain, and quality of life will be administered at baseline, 6-weeks, 12-weeks, and 30-weeks follow-ups (**Fig 1)**.

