#### Outcome measures and assessments

For the effectiveness trial, change in PTSD symptoms is the primary outcome measure (**Table 4**). Changes in depressive, pain, anxiety symptoms and quality of life are exploratory outcome measures.

**Table 4 pone.0275774.t004:** Primary and exploratory outcome measures for the effectiveness evaluation.

Outcome Measure	Explanation
Change in PTSD symptoms *Primary*: Change in PCL-5 scores from baseline to post-treatment (6-weeks).	The PCL-5 is a well-validated, widely used, and easy to administer 20-item self-report scale that is widely used in PTSD research and clinical practice [47]. Responses to each item relate to the four symptom clusters for PTSD, for which separate scores can be measured and used for additional analyses. The PCL-5 will be used for follow-up assessments over the CAPS-5 because of the feasibility of a self-report measure over a semi-structured interview and to reduce the reporting burden on participants.
*Exploratory*: Prolonged changes in PCL-5 scores from baseline to 12-week follow-up and 30-week follow-up.	
Change in depressive symptoms *Exploratory*: Change in depressive symptoms as measured by the nine-item Patient Health Questionnaire (PHQ-9) scores from baseline to 6-weeks, 12-weeks, and 30-weeks follow-ups.	PHQ-9 is a well-validated and widely used self-report scale used in depression research. Each item is rated on a 4-point scale for how much it bothered the participant in the past 2 weeks. A self-report scale is more feasible than an assessor-rated scale (e.g. HAM-D17) given the virtual nature of this study.
Change in pain symptoms *Exploratory*: Change in pain symptoms as measured by the Brief Pain Inventory (BPI) from baseline to 6-weeks, 12-weeks, and 30-weeks follow-ups.	BPI is a validated self-report scale used in pain trials and clinical pain practice and is a core outcome measure per the Initiative on Methods, Measurement, and Pain Assessment in Clinical Trials (IMMPACT) recommendations [50]. Two independent and clinically relevant measures are included: pain severity and pain interference with function.

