## Data analysis

### Sample size justification

The primary outcome is a continuous quantity measured using the PCL-5. The sample size is calculated to have 80% power at 5% type I error. Data from a previous waitlist control study of SKY gives us data to calculate an appropriate sample size. A study by Seppälä et al. used the PCL-M (a DSM-IV version of the PCL-5) for their primary outcome measures [29]. With a conservative standard deviation of magnitude 11 and an effect size of 5, 76 participants must be recruited in each group. A conservative dropout rate of 25% is projected for this study, which has been observed in other clinical trials for PTSD [4, 57]. Accounting for this expected dropout rate, 200 participants will be recruited, with 100 in each group.

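### The 6-week comparison is partially nested, because only the active arm is treated in groups of 8–12, yet neither the sample size nor the stated primary model allows for within-group correlation

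*Protocol article*

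**What the plan says.** Randomisation is of individuals: "Randomization will be performed with a 1:1 allocation to either the active intervention or waitlist control group" (Trial design). Treatment is then given in groups: "Participants randomized to the active arm will receive the v-SKY intervention in groups of 8–12" (Randomization and allocation). Each group shares 15 instructor-led sessions totalling 25 hours, with discussion of experiences at every session. The Introduction describes complementary and integrative interventions as a class as "complex interventions that involve numerous components such as meditation and breathing exercises, psychoeducation, and group dynamics".

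The primary outcome is the change in PCL-5 from baseline to 6 weeks (T2). Under Trial design, the waitlist arm starts v-SKY only after the T2 data collection.

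The Sample size justification section says "The sample size is calculated to have 80% power at 5% type I error" and "With a conservative standard deviation of magnitude 11 and an effect size of 5, 76 participants must be recruited in each group". It adds "A conservative dropout rate of 25% is projected for this study" and concludes that "200 participants will be recruited, with 100 in each group". No ICC or design effect is mentioned.

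The Effectiveness section under Data analysis names repeated measures analysis of variance, adjusted for baseline and for any significant confounders. It lists no term for delivery group, cohort or instructor.

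**The concern.** People who share an instructor, a set of sessions and a discussion group may end up with more similar outcomes than people who do not. At T2 this can happen only in the active arm, so the primary comparison is partially nested: grouped observations on one side and single ones on the other. An analysis that treats all participants as independent then understates the variance of the active-arm mean.

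The primary test is at stake. With positive within-group correlation its confidence interval is too narrow and its error is in the direction of declaring an effect. The stated 80% power also carries no allowance for group delivery.

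**Working it through.** **Inputs from the article:** difference 5, SD 11, 80% power, 5% type I error, 76 per arm, 25% dropout, 100 recruited per arm, groups of 8–12.

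**Assumptions:** a two-sided test (not stated, but a one-sided test would give 60 per arm); 10 active groups of 10, so 7.5 evaluable per group after 25% loss; ICC from 0.01 to 0.10; where baseline adjustment is shown, a baseline-to-T2 correlation of 0.5.

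**Step 1: the article's figure.** n = 2 × (1.960 + 0.842)² × 11² / 5² = 75.98, so 76. This is the independent-data formula with a design effect of 1. There is no slack in it: 100 × 0.75 = 75 evaluable per arm, which gives 79.5% power by the normal approximation at ICC 0.

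**Step 2: standard error and type I error.** The active-arm design effect is DE = 1 + (7.5 − 1) × ICC. The naive standard error is 11 × √(2/75) = 1.796 and the true one is 11 × √((DE + 1)/75). Their ratio is √((DE + 1)/2). The actual two-sided type I error is 2 × (1 − Φ(1.96/ratio)).

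**Step 3: power when group is modelled.** Noncentral t with noncentrality 5/SE and Satterthwaite degrees of freedom (Va + Vc)² / (Va²/9 + Vc²/74), where Va = 121 × DE/75 and Vc = 121/75. For baseline adjustment, both variances are multiplied by 1 − 0.5² = 0.75.

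Worked case, ICC 0.05: DE = 1.325; Va = 2.138; Vc = 1.613; SE = √3.751 = 1.937; ratio = 1.937/1.796 = 1.078; type I error = 2 × (1 − Φ(1.818)) = 6.9%. Degrees of freedom = 14.07/(0.508 + 0.035) = 25.9; noncentrality = 5/1.937 = 2.58; power = 70%. With baseline adjustment SE = 1.677, noncentrality = 2.98 and power = 82%.

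| ICC | DE | True/naive SE | Type I error, group ignored | df | Power, group modelled, no baseline adjustment | Power, group modelled, baseline-adjusted |
|---|---|---|---|---|---|---|
| 0 | 1.000 | 1.000 | 5.0% | 32 | 77% | 88% |
| 0.01 | 1.065 | 1.016 | 5.4% | 31 | 76% | 86% |
| 0.02 | 1.130 | 1.032 | 5.8% | 29 | 74% | 85% |
| 0.05 | 1.325 | 1.078 | 6.9% | 26 | 70% | 82% |
| 0.10 | 1.650 | 1.151 | 8.9% | 22 | 64% | 76% |

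**Step 4: sensitivity to group size.** Groups of 8–12 less 25% leave 6–9 evaluable. At ICC 0.05, type I error is then 6.5–7.4% and unadjusted power 72–68%. At ICC 0.10 they are 8.0–9.8% and 67–60%.

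**Step 5: the naive test at the planned effect.** Without baseline adjustment, the analysis that ignores group rejects in about 79%, 79%, 78% and 76% of trials at ICC 0.01, 0.02, 0.05 and 0.10. Keeping the naive test therefore costs mainly type I error, and the larger loss of power appears only once group is modelled.

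All of this applies to T2. By T3 and T4 the waitlist arm has also been treated, presumably in groups, so both arms would then be affected.

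**The case against.** A reader might infer that the trial definitely misses its 80% power. The documents do not support this. The comparison is planned with baseline adjustment, and at an assumed correlation of 0.5 power stays above 80% at ICCs up to 0.05. At that correlation the 25% variance gain is the same whether SD 11 refers to raw or to change scores. The 76–64% figures describe an analysis without the planned adjustment. Part of their shortfall is not correlation at all: power is already 77% at ICC 0, because of the degrees of freedom and because 75 rather than 76 per arm are evaluable. This objection stands, but it concerns power only. Baseline adjustment does not repair a standard error that ignores grouping.

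A reader might also infer that type I error is inflated even if v-SKY does nothing for anyone. It is not. Participants are randomised individually, and under that null, attending in groups induces no correlation and the naive test is valid. The inflated figures need a zero average effect with some groups doing better and others worse. This condition also stands.

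The ICC is assumed throughout. A standardised intervention and certified instructors with extra veteran-specific training could keep it small, and at 0.01 the harm is slight. Nothing in the article supports setting it to zero, though.

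Finally, the analysis plan is not shown and could contain a group effect. That is a fair caution about the model. But the article itself fixes the sample size under independence and names the primary model with its adjustments, and neither allows for group delivery.

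**Conclusion.** The point holds. The T2 comparison is partially nested, 76 per arm assumes independent observations, and the stated model has no delivery-group term. Any positive within-group correlation makes the T2 standard error too small, always in the anti-conservative direction.

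The size depends on an ICC that the documents do not give. Over 0.01–0.10 the true standard error is about 2–15% larger than the naive one, and type I error is about 5.4–8.9% under the null of zero average effect with variation between groups. The 80% power is uncertain rather than missed: about 86–76% with baseline adjustment at an assumed correlation of 0.5, and 76–64% without it. The type I and power losses are alternatives rather than a sum, since the first arises if group is ignored and the second if it is modelled. This should be fixed, but it does not invalidate the design.

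**What to change.** Fit the primary T2 contrast with a random intercept for SKY delivery group in the active arm, each waitlist participant being a singleton at T2, and use Satterthwaite or Kenward-Roger degrees of freedom, because there are only about 10 active groups. In the sample size section, replace the unqualified 80% with power over an explicit ICC range, and show the gain from baseline adjustment and the correlation it assumes.

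The cost is wording in the sample size and analysis sections. Group membership should be recoverable, since attendance logs are kept for each cohort. The downside is slightly wider intervals and a qualified or less favourable power figure. No extra participants are needed.
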